#### Interim analyses {21b}

No interim analysis is planned in this study. Safety of the interventions will be monitored by registering (serious) adverse events. In accordance with Section 10, subsection 4, of the WMO, the sponsor will suspend the study if there is sufficient ground that continuation of the study will jeopardise the subject health or safety.

#### Methods for additional analyses (e.g. subgroup analyses) {20b}

No subgroup analysis will be performed in this study.

#### Methods in analysis to handle protocol non-adherence and any statistical methods to handle missing data {20c}

In the event of missing data, this will be dealt with accordingly using additional statistical analyses (e.g. imputation). The primary analysis will be an intention-to-treat analysis. Every patient who has received at least one dose of study medication will be included in the ITT analysis.

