## Trial design {8}

This is a study protocol for a phase III, multicentre, open-label (i.e. non-blinded) randomised, controlled superiority trial, with parallel group assignment and 1:1 allocation. The protocol is written in accordance with the Standard Protocol Items: Recommendation for Interventional Trials (SPIRIT) guidelines [15]. Figure 1 shows a schematic diagram of the trial as the SPIRIT figure.

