### Participant timeline {13}

A schematic overview of study visits and assessments is shown in Table 1. The total duration of the study will be the undefined period of time between screening and the start of the investigative product and 12 months of follow-up.

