### Assignment of interventions: blinding

#### Who will be blinded {17a}

The design of this study is open-label. This entails that only the outcome assessors will be blinded during analyses. The assigned study arm will be known for both patients and all research staff (including the primary caregiver and principal investigator).

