### Statistical methods

#### Statistical methods for primary and secondary outcomes {20a}

Intention-to-treat analysis will be used throughout the study for primary and secondary endpoints. All randomised patients will be included in the intention-to-treat analysis. CR at 12 months will be reported as percentage. A Kaplan–Meier survival analysis with log-rank test will be performed to assess the rapidity of reaching CR. Time to CR will be censored at 12 months. In the unlikely event that a subject is withdrawn from the study due to liver-related mortality or liver transplantation, a competing risk analysis according to Fine and Gray will be performed.

All parameters will be summarised by the treatment group using descriptive statistics. Mean, standard deviation, median and range will be used for continuous variables. Counts and percentages will be used for categorical variables. For normally distributed continuous variables, Student’s *T*-test will be used, for not normally distributed continuous variables Mann–Whitney *U* test will be used. For categorical variables, the chi-square test or Fisher exact test will be used. For repeated measurements, paired *T*-test and Wilcoxon signed rank test will be used where appropriate. Confounding will be tested where appropriate.

The economic evaluation comparing the MMF and TAC policies will include a trial-based cost-effectiveness analysis (1-year healthcare costs per complete biochemical remission) and a model-based cost-utility analysis (life-long societal costs per QALY, calculated from the EQ-5D-5L).

Statistical analyses will be performed with Statistical Package for Social Sciences (SPSS), version 24.0 or higher. Two-sided tests will be used and* p*-values < 0.05 will be deemed significant.

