However, some important limitations of this trial must be considered. A multicentric set-up is required to reach complete recruitment. Administrative affairs may cause delays in opening study sites, limiting enrolment. After starting as a national study, an international extension of the study might be preferable. Furthermore, the open-label set-up may introduce some form of recall bias. Additionally, TAC, and especially Envarsus, is not always available at all sites. Consequently, different forms of TAC may be used throughout the study. Additionally, experience with TAC in non-transplant centres is limited. Therefore, it is possible that these study centres may be reluctant to include patients in the study. Active involvement of the coordinating investigator may encourage less experienced study sites to include participants. Lastly, recruiting hospitals are given the opportunity to refer patients to participating sites for study visits only (T0, T24, T52). This study set-up may simplify participation for patients who prefer their own treating physician.

In conclusion, this study should answer the question whether TAC or MMF is the second-line drug of choice, in combination with glucocorticoids, in case of not reaching CR on first-line therapy in AIH. The findings of this study are expected to inform the current clinical practice guidelines on the management of patients with AIH and incomplete CR to standard therapy.

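### The intention-to-treat set for the primary analysis is defined in two ways, all randomised patients and patients with at least one dose, and nothing says which governs

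*Protocol article*

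**What the plan says.** Two sections of the protocol article describe the same named analysis set.

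- Statistical methods for primary and secondary outcomes {20a}: "Intention-to-treat analysis will be used throughout the study for primary and secondary endpoints", followed by "All randomised patients will be included in the intention-to-treat analysis".
- Methods in analysis to handle protocol non-adherence and missing data {20c}: "The primary analysis will be an intention-to-treat analysis", followed by "Every patient who has received at least one dose of study medication will be included in the ITT analysis".

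Neither section calls the dosed set a modified ITT or safety set, and neither refers to the other. Who will be blinded {17a} states that patients and all research staff know the assigned arm; only the outcome assessors are blinded. Trial design {8} describes a "randomised, controlled superiority trial, with parallel group assignment and 1:1 allocation".

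**The concern.** A patient who is randomised and never takes study medication is in the primary analysis under {20a}. Under {20c}, read as a definition, that patient is not. In an open-label trial the decision not to start can be taken with the allocation known, so removing such patients is a selection made after randomisation. If it happens more in one arm, or for different kinds of patient in the two arms, the groups compared are no longer the groups that were randomised.

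There is also a question of pre-specification. With both rules in print, the denominator of the primary comparison could be settled after the data are seen, and either choice could be defended from the text. Because {20a} applies ITT to primary and secondary endpoints, the ambiguity reaches both.

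**Working it through.** **Step 1: do the two rules describe the same set?** Let R be the randomised patients and D those who took at least one dose, with D contained in R. Section {20a} sets ITT = R. Section {20c}, read as a definition, sets ITT = D. They are equal only if nobody fails to start. Read as nested (D is included, and so is everyone else in R), the one-dose condition has no effect, because R already contains D.

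**Step 2: the plan's own figure, as the base.** Sample size {14} gives complete response (CR) proportions of 0.22 (MMF) and 0.53 (TAC), two-sided alpha 0.05 and power 0.80. The two-proportion formula with pooled variance, mean proportion 0.375, gives

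n = [1.960·√(2·0.375·0.625) + 0.842·√(0.22·0.78 + 0.53·0.47)]² / 0.31² = 37.1, so 38 per arm.

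With 10% loss, 38/0.9 = 42.2, so 43 per arm and 86 in total. This matches the plan. The contradiction does not depend on it; it only fixes the arm size used below.

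**Step 3: what a few non-starters could do.** The protocol gives no non-start rate. The counts below are assumptions, and every excluded patient is taken to be a non-responder. The test is Pearson chi-square without continuity correction, X² = N(ad − bc)² / (product of the four margins), where a and b are responders and non-responders on TAC, and c and d those on MMF.

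| Scenario | TAC | MMF | Difference (points) | X² | p |
|---|---|---|---|---|---|
| All randomised | 19/43 | 11/43 | 18.6 | 3.28 | 0.070 |
| 2 undosed TAC excluded | 19/41 | 11/43 | 20.8 | 3.94 | 0.047 |
| 4 undosed TAC excluded | 19/39 | 11/43 | 23.1 | 4.72 | 0.030 |
| 2 undosed excluded in each arm | 19/41 | 11/41 | 19.5 | 3.36 | 0.067 |
| Near the planned effect, all randomised | 23/43 | 9/43 | 32.6 | 9.76 | 0.002 |
| Near the planned effect, 4 undosed TAC excluded | 23/39 | 9/43 | 38.0 | 12.44 | 0.0004 |

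First row in full: ad − bc = 19·32 − 24·11 = 344, and 86·344² / (43·43·30·56) = 3.28.

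**Step 4: sensitivity to the test.** For 19/39 against 11/43, continuity correction gives p = 0.052 and Fisher's exact test p = 0.040. For 19/41 against 11/43, Fisher gives p = 0.068. Whether a borderline result crosses 0.05 therefore depends on the test as well as on the assumed counts.

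**The case against.** The best defence is that {20c} says who is included and never says that undosed patients are excluded. Under a heading on non-adherence it could mean that even a single dose keeps a non-adherent patient in the analysis, and {20a} would then be the exhaustive rule. That reading is possible, and no sentence prescribes exclusion. But it leaves the one-dose condition without function, and the sentence directly follows the statement that the primary analysis is ITT. An analyst could take it as the definition of the set.

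The objection to the size stands. The numbers in the working are chosen near the significance threshold, and the conclusion changes only when the excluded patients fall in one arm. Nothing in the documents shows that anyone will fail to start.

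A reader might go further and infer that the plan itself names reasons for TAC patients in particular not to start. The documents do not support that:

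- The Discussion says "TAC, and especially Envarsus, is not always available at all sites", but gives the consequence as use of other TAC formulations, which Intervention description {11a} also allows. The documented response to shortage is substitution.
- The same section describes centres with little TAC experience as possibly reluctant to include patients. That acts before randomisation and so on both arms alike.
- Participant timeline {13} mentions "the undefined period of time between screening and the start of the investigative product". That interval begins at screening and does not describe the time from randomisation to first dose.

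Nor is a higher TAC response rate under a dosed-only set a certainty: it requires that the excluded TAC patients respond less often than those who start.

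**Conclusion.** The point holds as an internal contradiction: one named analysis set, two membership rules, no order of precedence. Both rules are printed in the article, so this is not a detail left to a fuller document. Taken as a definition, the {20c} sentence is a modified ITT rule and is unsuitable as the primary population of an open-label superiority trial, because it permits exclusions after allocation is known.

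The bias is possible, not shown. It is zero if every randomised patient starts, and otherwise its direction and size rest on assumptions about how many do not start, in which arm, and how they would have responded. In the assumed one-sided scenarios, two to four patients move a borderline p from 0.070 to 0.047 or 0.030. With balanced non-starting, or an effect near the planned one, the conclusion is unchanged. It should still be corrected before analysis, because it fixes the primary denominator. A change to when the 12-month clock starts does not follow from this contradiction and forms no part of the point.

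**What to change.** Replace the one-dose sentence in {20c} with the rule in {20a}: for primary and secondary endpoints the ITT set is every randomised patient, analysed in the arm assigned, dosed or not. If a dosed-only set is wanted, give it its own name (safety set, or modified ITT for sensitivity analysis) and keep the one-dose condition there.

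The planned total of 86 and the study procedures do not change. Response rates may be slightly less favourable if some patients never start and do not reach CR. For example, with an assumed four undosed TAC non-responders and a CR rate of 0.53 among the 39 dosed, the all-randomised difference is 0.53·39/43 − 0.22 = 0.261 instead of 0.31, and approximate two-proportion power is 73%, against 84% with the dosed-only set. That is the price of keeping the randomised comparison, and it is nil if everyone starts. Trial status reports 5 of 86 patients randomised at the time of writing.

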#### Plans to give access to the full protocol, participant-level data and statistical code {31c}

After publication of the final manuscript, data may be available upon reasonable request. The dataset analysed during the current study and statistical code can then be requested through the principal investigator of the sponsor site, as is the full protocol.

### Oversight and monitoring

#### Composition of the coordinating centre and trial steering committee {5d}

Leiden University Medical Center is the coordinating centre of this study. Both the principal investigator and the coordinating investigator are employed by the coordinating centre. The coordinating investigator is responsible for the day-to-day support of participating and recruiting sites. Additionally, data collection and analyses will be done once the study is finished. The principal investigator is updated on the study weekly. Additionally, the Dutch Autoimmune Hepatitis Working Group (DAIHWG) is updated biannually on the study’s progress during meetings. The DAIHWG consists of hepatologists with an interest for AIH from various (study) sites.

#### Composition of the data monitoring committee, its role and reporting structure {21a}

It was not deemed necessary by the medical ethical committee to constitute an independent data safety management board for this study.

#### Adverse event reporting and harms {22}

AEs are defined as any undesirable experience occurring to a subject during the study, whether or not considered related to the investigational product. All adverse events reported spontaneously by the subject or observed by the investigator or his staff will be recorded. A SAE is any untoward medical occurrence or effect that (a) results in death; (b) is life-threatening (at the time of the event); (c) requires hospitalisation or prolongation of existing inpatients’ hospitalisation; (d) results in persistent or significant disability or incapacity; (e) is a congenital anomaly or birth defect; and (f) requires medical or surgical intervention to preclude of any other important medical event that did not result in any of the outcomes listed above due to medical or surgical intervention but could have based upon appropriate medical judgement. Elective hospital admissions are not considered SAEs. The principal investigator of the participating site will report the SAE to the coordinating investigator within 24 h. The latter will report the medical ethical committee via Toetsingonline.nl within 7 (death) or 15 (life threatening event) days.

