#### Intervention description {11a}

##### Group one: Prolonged-release tacrolimus (Envarsus®)

For this study, TAC will be used, preferably 0.75 mg, 1 mg and 4 mg tablets of Envarsus® from Chiesi Pharmaceuticals. Envarsus is a once-daily prolonged-release formulation with more stable tacrolimus levels [31, 32]. Patients in this arm will start with oral 0.07 mg/kg/day of meltdose tacrolimus once daily. If Envarsus is unavailable, other forms of TAC (e.g., Advagraf, Adport, Dailiport, Prograft) may be used, with the appropriate dosing scheme, since different forms of TAC have different bioavailability. Tacrolimus has a narrow therapeutic window and highly variable pharmacokinetics. Therapeutic drug monitoring (TDM) will be performed to reach a target AUC of 160 µg h/L (20% interval 128–196) tacrolimus. This is compatible with trough levels of 3.6–7.4 µg/l [33–35]. Tacrolimus can have several adverse effects. Due to a narrow therapeutic window, therapeutic drug monitoring is necessary to prevent underexposure, which can result in reduced effect, and overexposure, which can lead to side effects including hypertension, tremor, headache, renal toxicity and hyperkalaemia. Like with any other immunosuppressive drug, there is an increased risk of infections.

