##### Group 2: mycophenolate mofetil (Cellcept®)

For this study, 500 mg tablets of CellCept® from F. Hoffmann-La Roche AG Pharmaceuticals will be used. If not available, generic forms of MMF may be used. Patients in the MMF arm will receive a maximum total dose of 2000 mg daily, split-dose. Patients will commence with a dose of 500 mg twice daily. When tolerated, doses will be titrated to 1000 mg twice daily after week 2. The most common adverse effects are gastrointestinal toxicity, leukopenia, thrombopenia and increased risk of infections.

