### Data collection and management

#### Plans for assessment and collection of outcomes {18a}

At the screening visit, data on demographics, medical history and medication use is collected after obtaining informed consent. Simultaneously laboratory assessments are done, including screening for systemic infections and pharmacogenetics, and VCTE is performed. After inclusion, participants visit the outpatient at different timepoints (Table 1). During these visits, laboratory tests are done, TDM is done using the area under the curve measurements (visits T_2_ and T_12_) or trough levels (only for TAC on visits T_24_, T_36_, T_52_), and (serious) adverse events ((S)AEs) are reviewed. During specified study visits, health-related quality of life (HRQoL) questionnaires are administered and VCTE is done.

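### Tremor and diarrhoea are named safety outcomes, but the stated adverse event capture in this open-label trial leaves them open to unequal detection between arms

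*Protocol article*

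**What the plan says.** All references are to the protocol article.

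- **Outcomes {12}, Secondary outcomes.** Tremor and diarrhoea are listed individually under safety and tolerability, with no instrument, question or grading scale given for either.
- **Adverse event reporting and harms {22}.** The capture rule is: "All adverse events reported spontaneously by the subject or observed by the investigator or his staff will be recorded".
- **Plans for assessment and collection of outcomes {18a}.** At study visits laboratory tests and drug monitoring are done "and (serious) adverse events ((S)AEs) are reviewed". What the review asks is not stated.
- **Who will be blinded {17a}.** "The assigned study arm will be known for both patients and all research staff (including the primary caregiver and principal investigator". As for assessors: "This entails that only the outcome assessors will be blinded during analyses".
- **Intervention description {11a}.** Tacrolimus overexposure can lead to "side effects including hypertension, tremor, headache, renal toxicity and hyperkalaemia". For MMF: "The most common adverse effects are gastrointestinal toxicity, leukopenia, thrombopenia and increased risk of infections".
- **Statistical methods {20a}.** "For categorical variables, the chi-square test or Fisher exact test will be used". A between-arm test of the two symptoms is therefore foreseen.

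**The concern.** Most neighbouring items in the safety outcome, such as creatinine, potassium, blood pressure and glucose, are measured values. Whether they are recorded does not depend on who mentions them. Mild tremor and loose stools are different: they reach the data set if the patient brings them up or someone notices or asks. The protocol pairs each symptom with one arm's expected profile and leaves detection to people who know the arm. Blinding assessors during analysis comes too late, because by then the symptom has or has not been recorded.

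If detection differs by arm, part of the observed contrast would reflect attention rather than drug effect. The expected direction is more recorded tremor on tacrolimus and more recorded diarrhoea on MMF. These contrasts matter for interpretation. The section on the choice of comparators {6b} says MMF might be preferred for its adverse effect profile even if it is less effective, and the Discussion expects the trial to settle which drug is the second-line choice. The Discussion concedes possible recall bias from the open-label design but does not mention unequal detection.

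**Working it through.** **1. What the documents supply.** They give no tremor or diarrhoea rate and no detection probability, so there is no plan figure to reproduce and the bias cannot be estimated from them. The only usable number is the arm size. The Sample size section {14} has 38 per group and 10% loss: 38 / 0.90 = 42.2, rounded up to 43 per group, 86 in total, as stated.

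**2. The sections side by side.**

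| Question | Answer in the article |
|---|---|
| Are the two symptoms separate outcomes? | Yes, {12} |
| How does an event enter the record? | Volunteered or observed, {22}; reviewed at visits, content unstated, {18a} |
| Is anyone blinded at that moment? | No; arm known to patients and staff, {17a} |
| Is each symptom tied to one arm? | Tremor to tacrolimus directly; diarrhoea to MMF through gastrointestinal toxicity, {11a} |
| Is a uniform question or grade stated? | No |

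These together allow unequal detection. They do not show that it occurs.

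**3. Illustration of size (assumed inputs).** Let p be the true rate, equal in both arms. Let s1 be the share of cases detected in the arm where the effect is expected, and s2 the share in the other arm.

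- Recorded rates: a = p × s1 and b = p × s2.
- Spurious risk ratio: a / b = s1 / s2, whatever the value of p.
- Spurious difference: a − b = p × (s1 − s2).

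The chance of p < 0.05 in the expected direction with n = 43 per arm, by normal approximation without continuity correction, is Φ{(a − b − 1.96 × SE0) / SE1}. Here SE0 = √[2m(1 − m)/n] with m = (a + b)/2, and SE1 = √[(a(1 − a) + b(1 − b))/n].

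Example with p = 0.20, s1 = 0.90, s2 = 0.50:
- a = 0.18, b = 0.10, ratio 1.80, difference 0.08.
- m = 0.14, SE0 = 0.0748, SE1 = 0.0743.
- (0.08 − 1.96 × 0.0748) / 0.0743 = −0.90, and Φ = 0.185.

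| True rate p | s2 | Recorded a vs b | Difference | Ratio | Chance of p < 0.05 |
|---|---|---|---|---|---|
| 10% | 70% | 9% vs 7% | 2 points | 1.29 | 5.3% |
| 20% | 70% | 18% vs 14% | 4 points | 1.29 | 7.3% |
| 30% | 70% | 27% vs 21% | 6 points | 1.29 | 9.5% |
| 40% | 70% | 36% vs 28% | 8 points | 1.29 | 12.1% |
| 10% | 50% | 9% vs 5% | 4 points | 1.80 | 10.8% |
| 20% | 50% | 18% vs 10% | 8 points | 1.80 | 18.5% |
| 30% | 50% | 27% vs 15% | 12 points | 1.80 | 27.4% |
| 40% | 50% | 36% vs 20% | 16 points | 1.80 | 37.7% |

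With equal detection (90% in both arms) the ratio is 1.00 and the chance is the nominal 2.5% in one direction. The plan also allows Fisher's exact test, which is more conservative at these counts and would lower the chances shown. It would not change the ratios.

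**4. In patients.** At a 20% true rate, 43 × 0.18 = 7.7 recorded cases compare with 43 × 0.14 = 6.0 or 43 × 0.10 = 4.3. The whole effect is about two to three patients.

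**The case against.** **A reader might infer that an event is recorded only if volunteered or seen.** The text does not say so. Section {22} sets a duty to record what is reported or observed; it does not rule out asking. Section {18a} has events reviewed at visits in both arms, so capture is not purely passive. This stands and softens the point. It does not remove it, because a review of unstated content by staff who know the arm leaves the same route open.

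**A reader might infer that each drug's expected effect will be over-detected in its own arm.** The documents do not support that certainty. They give no rates, and the illustrative ratios follow entirely from the chosen detection shares. The equal-true-rate premise is itself only a device, since the protocol expects tremor on tacrolimus. The link from diarrhoea to MMF is indirect.

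**The detail may exist elsewhere.** Listing the two symptoms separately fits dedicated data collection as well as it fits general adverse event capture. The content of Table 1, the eCRF and the full protocol were not available for this review, and any of them could hold a symptom checklist. This also stands, so the fix is conditional. The point survives because the article is not silent on capture: it states a rule, and that rule suits these two outcomes poorly.

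**The importance is limited.** These are two items within one secondary outcome. The feared biases run in opposite directions, one against each drug, so no net distortion of the overall trade-off is shown. Uniform questions would also leave answers and grades open to expectation. All of this is correct. It bounds the point, but each symptom contrast would still be hard to interpret on its own.

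**Conclusion.** The concern holds as a risk of unknown size. Tremor and diarrhoea may be differentially detected between arms, because the stated capture depends on volunteering, observation and an unspecified review by people who know the treatment, and each symptom matches one arm's expected profile. The spurious risk ratios of 1.29 and 1.80 are illustrations. They assume an equal true rate in both arms, 90% detection in the arm where the effect is expected, and 70% or 50% in the other. They are not estimates for this trial.

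The conclusion also assumes that no uniform questioning is already laid down in Table 1, the eCRF or the full protocol. If it is, only a clarifying sentence is needed. The complete biochemical response endpoint rests on ALT, AST and IgG, so neither it nor its sample size is touched.

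**What to change.** First check whether the visit schedule or eCRF already asks about both symptoms identically in both arms. If so, say so in {18a} or {22}. If not:

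- At baseline and every scheduled visit, ask the same short fixed questions on tremor and diarrhoea in both arms: present or absent, and severity grade. Include the visits that referred patients make at recruiting centres.
- Base the two between-arm comparisons on these solicited answers.
- Keep the rule in {22} for all other adverse events.

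**Cost.** A few eCRF items at visits that already take place. Absolute rates of mild tremor and diarrhoea will be higher than under spontaneous reporting. The 5 patients already randomised when the article was written, of 86 planned, will lack the baseline items. Some open-label reporting bias will remain, because patients and staff still know the arm when they answer and grade, and the report of results should acknowledge it.
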